### Sample size

The sample size calculation is based on the results of trials by Li et al. [18] and Ji et al. [19] and the recommendation of acupuncture specialists in China. The mean value of the NDI score in the 2.5 Hz group is 82.28, the standard deviation is 6.97; the mean value of the NDI score in the 2 Hz group is 86.73, the standard deviation is 7.10; the mean value of the NDI score in the 1 Hz group is 76.50, the standard deviation is 8.06; the mean value of the NDI score in the control group is 65.85, the standard deviation is 16.47. To detect a significant difference between any two groups with a power of 90% and a type I error of 5%, the calculated number of patients is 17. Considering a 30% dropout rate, the total sample size required is 88 patients.

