#### MA manipulation groups A, B, and C

The main acupoints ST36, PC6, and RN12 will be needled in each group. Additional acupoints will also be used based on symptom differentiation. For stagnation of liver qi, RN17 and LR13 (bilateral) are added; for deficiency of spleen qi and stomach qi, one adds BL20 (bilateral) and BL21 (bilateral); for stomach disorder due to liver qi, LR14 (bilateral) and LR3 (bilateral) are added; for damp heat in middle Jiao, one adds SP9 (bilateral) and ST44 (bilateral). Acupoints will be localized according to the 2008 World Health Organization standards [12]. Sterilized stainless steel needles (Φ0.25 mm × 25 mm or 0.25 mm × 40 mm, Tianjin Hua Hong Medical Co., Ltd., Tianjin, China) will be used for all acupuncture procedures. The length of the needle will be chosen according to the acupoint.

After a *de qi* sensation is achieved, the needles in MA manipulation groups A, B, and C will be respectively manipulated manually with three different frequencies (1, 2, or 3 Hz) of lifting-inserting MA manipulations (see Table 1). The lifting-inserting MA manipulation procedure is shown in Fig. 2. Briefly, after *de qi*, the lifting-inserting MA manipulation will be performed for 1 minute, three times, separated by 10-minute intervals. The entire procedure takes 33 minutes. The acupuncture treatment consists of 10 sessions over a period of 2 weeks (one session per day, five continual sessions per week, with a 2-day interval between the 2 weeks) after randomization. All participants will be followed up three times in 10 weeks after treatment (at 4, 8, and 12 weeks).

**Table 1 Tab1:** Parameters of three different lifting-inserting MA manipulations in MA manipulation groups

MA manipulation group	Frequency (Hz)	Operation of MA	Depth (mm)	Duration (s)
Group A	1	Neutral reinforcement and reduction	2–3	60
Group B	2			
Group C	3			

*MA* Manual acupuncture

In neutral reinforcement and reduction, the needle is perpendicular to the skin, and the force and amplitude of the lifting-inserting displacement is uniform; the lifting-inserting distance is 2–3 mm

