#### Primary outcomes

Patients’ response to the treatment will be measured by an improved response rate (IRR) [13]: for EPS, the improvement of at least two scores and/or no occurrence of epigastric pain and epigastric burning included in the scale are regarded as positive responses. The Symptom Index for EPS is a 4-indicator scale assessing two main dyspepsia symptoms (epigastric pain and epigastric burning) with a scale ranging from 0 to 3. A score of 0 indicates symptoms not present; 1 indicates occasional and mild symptoms that do not interfere with social activities; 2 indicates prolonged and obvious symptoms interfering with work or rest; and 3 indicates severe symptoms with an impact on work or rest. The IRR is the percentage of patients who are symptom-free or have shown improvement in at least two scores at the end of the treatment and follow-up.

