#### Secondary outcomes

Dyspeptic symptoms will be assessed by the Chinese version of the Nepean Dyspepsia Index (NDI) [14], including the intensity, frequency, and level of interference of postprandial fullness, early satiety, epigastric pain, and epigastric burning sensation. The intensity of each symptom is graded and scored as follows: 0, absent; 1, mild; 2, moderate; 3, severe; 4, critical. The frequency of each symptom is also graded: 0, absent; 1, occasionally (1–2 days/week); 2, sometimes (3–5 days/week); 3, frequently (every day, but intermittent symptoms); 4, continuous symptoms. The level of interference of each symptom is scored and graded as follows: 0, none; 1, mild interference; 2, moderate interference; 3, severe interference; 4, critical interference. The number in front of each grading indicates the score of the corresponding symptom; the score for each symptom in the checklist of cardinal dyspeptic symptoms is calculated by adding its scores in the corresponding frequency, severity, and level of discomfort. The dyspeptic symptom sum score (DSSS) is the sum score of the four symptoms in the checklist.

The quality of life will be evaluated by the Short-Form 36 questionnaire (SF-36) [15]. Mental status will be measured by the Zung Self-Rating Depression Scale (SDS) [16] and Self-Rating Anxiety Scale (SAS) [17]. The SF-36 measures quality of life (QoL) across eight domains; the score of each domain = [(actual raw score − lowest possible raw score)/raw score range] × 100. For the SDS score, the following equation is used: SDS Index = Raw Score × 1.25. The grading of the SDS is as follows: SDS Index less than 53 points is considered normal, 53–62 is considered mild depression, 63–72 as moderate depression, and 73 and higher as severe depression. For SAS grading, the following categories are used: normal range (less than 50), mild anxiety (50 to 59), moderate anxiety (60 to 69), and severe anxiety (70 and higher).

Fasting serum levels of gastrin, motilin, and ghrelin will be measured by the enzyme-linked immunosorbent assay. A fasting venous blood sample will be drawn from the basilic vein prior to breakfast early in the morning before and after treatment.

Any adverse reactions of patients will be recorded in the case report form (CRF), including swelling, pain, bruise at the sites of needle insertion, or discomfort, palpitation, dizziness, etc., after acupuncture.

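### The sample size and its 90% power rest on NDI means, not on the binary primary outcome; the means exceed the only NDI total the trial defines and do not give 90% for any two groups

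*Protocol article*

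**What the plan says.** All references are to the protocol article.

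- **Primary outcome.** Under Primary outcomes, response to treatment "will be measured by an improved response rate (IRR"), the share of patients who are symptom-free or improve by at least two scores on the EPS Symptom Index. It is a proportion.
- **Secondary outcome.** The NDI appears under Secondary outcomes. Four symptoms are each scored 0 to 4 for intensity, frequency and interference, and "The dyspeptic symptom sum score (DSSS) is the sum score of the four symptoms in the checklist". No other NDI total is defined.
- **Sample size.** The inputs are means and standard deviations of an NDI score. The first reads "The mean value of the NDI score in the 2.5 Hz group is 82.28" (SD 6.97). The others are 86.73 (SD 7.10) for 2 Hz, 76.50 (SD 8.06) for 1 Hz and 65.85 (SD 16.47) for control. The aim is "To detect a significant difference between any two groups with a power of 90" percent at a 5% type I error. The result is 17 patients, and 88 in total after a 30% dropout allowance.
- **Arms.** Treatment uses "three different frequencies (1, 2, or 3 Hz) of lifting-inserting MA manipulations", plus a control group needled without manipulation. There is no 2.5 Hz arm.

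**The concern.** A power figure belongs to the endpoint, effect size and variability that produced it. Here these come from a continuous score listed as secondary, while the trial will be judged on a difference in response proportions. The article assumes no response rate, so nothing in it says what IRR difference 88 patients can detect.

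The NDI figures are also hard to attach to the secondary endpoint. They lie above the range of the one NDI total described, and the section does not say which NDI score they are or which direction is favourable.

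The stake is how a null primary result is read. A reader who meets the only power statement in the article may take it as covering the main result, and may then read an imprecise finding as evidence that frequency does not matter.

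**Working it through.** **1. The plan's total.** Reading 17 as per group: 17 × 1.3 = 22.1, taken as 22; 22 × 4 = 88. The total follows by multiplying up.

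**2. The plan's 17.** Inputs are the means and SDs in the Sample size section. Sidedness is not stated, so two-sided 0.05 is assumed, without multiplicity adjustment. For each pair, d is the difference in means and s² the average of the two variances:

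- n per group = 2(1.960 + 1.282)² s²/d²
- power at n = Φ(d/(s√(2/n)) − 1.960)

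| Pair | d | s | n for 90% | Power at 17 |
|---|---|---|---|---|
| 2.5 vs 2 Hz | 4.45 | 7.04 | 53 | 45% |
| 2.5 vs 1 Hz | 5.78 | 7.53 | 36 | 61% |
| 1 Hz vs control | 10.65 | 12.97 | 32 | 67% |
| 2.5 Hz vs control | 16.43 | 12.65 | 13 | 97% |
| 2 vs 1 Hz | 10.23 | 7.60 | 12 | 98% |
| 2 Hz vs control | 20.88 | 12.68 | 8 | 99.8% |

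Worked case, 2.5 vs 2 Hz: s² = (6.97² + 7.10²)/2 = 49.5; n = 2 × 10.51 × 49.5/4.45² = 52.5, so 53. At 17, the standard error is 7.04 × √(2/17) = 2.41, and Φ(4.45/2.41 − 1.96) = 45%.

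Covering every pair needs 53 per group. The t-distribution lowers the three weak powers slightly, to 43%, 58% and 64%. A four-arm overall ANOVA needs 8 per group. The figure 17 appears only in isolated variants that the article does not state: 2 vs 1 Hz with Bonferroni for six pairs, 2.5 Hz vs control with Bonferroni for three, and 1 Hz vs control one-sided with the SD pooled over four arms. None covers all pairs.

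**3. Range of the defined NDI total.** Four symptoms × three dimensions × a maximum of 4 = 48, with higher meaning worse. The article does not print 48; it follows from the scoring rules. The lowest planning mean, 65.85, is already above it.

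**4. What the trial can detect on the IRR.** The article gives no rates, so those below are assumptions. They refer to one pair of arms at two-sided 0.05. The required size, with p̄ the mean of the two proportions, is

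n per arm = [1.960√(2p̄(1−p̄)) + 1.282√(p₁(1−p₁) + p₂(1−p₂))]² / (p₁−p₂)²

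- 40% vs 90%: 16.9, so 17 per arm.
- 40% vs 86%: 21.0, which 22 per arm meets (exact power 91%). 40% vs 85% gives 22.2, just short.
- 50% vs 80%: 51.0, so 52 per arm.

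Power of the Pearson test by exact enumeration of both binomials:

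| Assumed IRR | 17 per arm | 22 per arm |
|---|---|---|
| 50% vs 80% | 46% | 55% |
| 40% vs 70% | 45% | 52% |
| 60% vs 80% | 23% | 30% |

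**The case against.** Several points on the other side are fair.

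- **The article never ties 90% to the IRR.** A reader might infer that it claims 90% power for the primary outcome. It does not; the sentence concerns NDI scores. The accurate criticism is that no power is given for the primary outcome and that the figure given does not carry over.
- **The NDI is a named outcome, and the Sample size section says NDI score, not DSSS.** A reader might conclude that the figures come from another scale, or that they show control doing best. Neither can be established. The two source trials are not available here, and reading control as best imposes the DSSS direction on values that cannot be DSSS values. What stands is that the figures lie outside the defined range and come without a subscale or direction.
- **Borrowing the nearest available frequency is ordinary practice.** Four figures for four arms suggest that 2.5 Hz stands in for 3 Hz, but the article does not say so. This is a gap in labelling and plays no part in the endpoint mismatch.
- **The phrase about any two groups could mean at least one pair.** On that reading 17 is enough, since three pairs exceed 90%. But the Hypothesis section expects high frequency to beat low, and the planning figures give 61% for the highest against the lowest frequency.
- **All response rates above are assumed, and ITT with LOCF makes 22 per arm arguably the relevant number.** Both points are accepted, which is why both sizes are shown. With 22 per arm, a 30-point difference in these examples still has only 52% to 55% power. A null result would be imprecise, though calling it uninformative would go too far.

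**Conclusion.** The concern holds. The decisive fault is the endpoint mismatch: the 90% is derived from a continuous secondary measure and does not cover the binary primary comparison. Two further faults affect the NDI statement itself. Its means exceed the 48-point maximum of the only NDI total defined, so they cannot be applied to that score as written. And at 17 per group, its own means and SDs give about 45% (2.5 vs 2 Hz), 61% (2.5 vs 1 Hz) and 67% (1 Hz vs control).

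For the IRR, 90% power requires a gap of roughly 46 points from a 40% base with 22 per arm, or 50 points with 17. The NDI powers assume two-sided 0.05, no multiplicity adjustment and 17 read as per group. The IRR powers rest also on the assumed response rates; other base rates would shift them. The range argument depends only on the scoring rules under Secondary outcomes.

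**What to change.** Keep 88 patients and rewrite the Sample size paragraph.

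1. State the IRR difference detectable with 22 randomised and about 17 evaluable per arm, under named assumed control rates and test sidedness. For example, at two-sided 0.05, 90% power needs about 40% vs 86% with 22 per arm or 40% vs 90% with 17, and 50% vs 80% has about 55% or 46%.
2. Say plainly that the 90% does not refer to the primary outcome.
3. Withdraw the NDI statement about any two groups, or restate it pair by pair with the NDI scale and its direction named and 2.5 Hz labelled as a proxy for 3 Hz. It should not be offered as power for the DSSS: relabelling it as support for that secondary endpoint would keep values the score cannot take and a 90% that three of the six pairs do not reach.

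The cost is one paragraph and a less favourable power statement. No patients, arms or procedures change. Recruitment was ongoing at publication, so the correction is best made before the results are analysed.

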### Hypothesis

Based on our previous study, our hypothesis is that MA manipulations with different frequencies have different effects on dyspepsia symptoms and quality of life, and that the high frequency will have a better effect than the low frequency.

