### Statistical analysis

The statistical analysis will be performed by two independent statisticians. The statisticians are blinded to treatments and study protocol. Statistical analysis will be conducted on the basis of an intention-to-treat (ITT) analysis. Missing values will be imputed by the last observation carried forward (LOCF) method. Categorical data will be analyzed with the McNemar chi-square test. Continuous data will be analyzed by analysis of variance (ANOVA). If the data trend over time and over time by treatment interactions, the repeated-measures ANOVA will be used. A *P* value less than 0.05 is regarded as statistically significant.

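### The 90% power claimed between any two groups at 17 patients per group holds for only three of the six pairs on the plan's own NDI figures; the other three have 43%, 58% and 63%

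*Protocol article*

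**What the plan says.** The Sample size section of the protocol article gives four planning means and SDs for the NDI. The list begins: "The mean value of the NDI score in the 2.5 Hz group is 82.28, the standard deviation is 6.97". The other three are 86.73 (SD 7.10) at 2 Hz, 76.50 (SD 8.06) at 1 Hz and 65.85 (SD 16.47) for control.

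The section then states the aim, "To detect a significant difference between any two groups with a power of 90% and a type I error of 5" per cent, and the result, "the calculated number of patients is 17". With 30% dropout the total becomes 88. The section names no formula, sidedness or multiplicity adjustment. The Statistical analysis section plans ANOVA for continuous data and says: "A *P* value less than 0.05 is regarded as statistically significant". The Hypothesis section expects that frequencies differ in effect and that "the high frequency will have a better effect than the low frequency".

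**The concern.** Read in the ordinary way, the sentence promises 90% power for each of the six pairwise comparisons among four groups. The six planning differences run from 4.45 to 20.88 NDI points, and the SDs from 6.97 to 16.47. A single sample size of 17 is unlikely to serve all of them.

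The stake is how a null result would be read. The trial asks whether frequencies differ from one another. A reader who trusts the power statement would take a non-significant contrast between two frequencies as fair evidence of little or no difference. If the contrast had about 50% power on the plan's own assumptions, that inference would not be justified.

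**Working it through.** **Inputs.** Means and SDs are those listed in the Sample size section. Alpha is 0.05, taken as two-sided and unadjusted because the article states neither sidedness nor an adjustment. Allocation is 1:1:1:1 (section on recruitment, randomization, allocation concealment and blinding).

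**Is 17 per group?** 17 × 1.3 = 22.1, and 22.1 × 4 = 88.4, which is the stated 88. So 17 is per group before dropout, and 22 per group are randomised.

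**Pairwise power.** For a pair with difference d and SDs s1 and s2, at n per group:

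- standard error = √[(s1² + s2²)/n]
- noncentrality = d / standard error
- Welch degrees of freedom = (n − 1)(s1² + s2²)² / (s1⁴ + s2⁴)
- power from the noncentral t distribution

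Example, 2.5 vs 1 Hz at n = 17:

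- d = 82.28 − 76.50 = 5.78
- s1² + s2² = 6.97² + 8.06² = 113.54
- standard error = √(113.54/17) = 2.584
- noncentrality = 5.78/2.584 = 2.24, with 31.3 degrees of freedom and critical value 2.04
- power = 58%

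| Pair | d | s1² + s2² | Power, 17 per group | Power, 22 per group | n per group for 90% |
|---|---|---|---|---|---|
| 2.5 vs 2 Hz | 4.45 | 98.99 | 43% | 54% | 54 |
| 2.5 vs 1 Hz | 5.78 | 113.54 | 58% | 70% | 37 |
| 1 Hz vs control | 10.65 | 336.22 | 63% | 75% | 33 |
| 2.5 Hz vs control | 16.43 | 319.84 | 95% | 99% | 14 |
| 2 vs 1 Hz | 10.23 | 115.37 | 97% | 99% | 13 |
| 2 Hz vs control | 20.88 | 321.67 | 99.6% | >99.9% | 10 |

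The closed form n = (1.960 + 1.282)² (s1² + s2²)/d² agrees: 52.5, 35.7, 31.1, 12.4, 11.6 and 7.8 in the same order. No pair gives 17.

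**Other choices of method.** At 17 per group the same three pairs stay below 90% in each case:

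- equal-variance t test: 43%, 58%, 64%
- normal approximation: 45%, 61%, 67%
- one-sided 0.05, t test: 56%, 71%, 76%

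With one common SD pooled over the four groups (10.43), four of the six pairs fall below 90%, at 23% to 83%. A multiplicity adjustment would lower power further.

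**Where 17 may come from.** For a four-group omnibus F test:

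- The grand mean is 77.84 and the deviations are 4.44 (2.5 Hz), 8.89 (2 Hz), −1.34 (1 Hz) and −11.99 (control).
- Their squares sum to 244.30.
- With the largest SD, 16.47, taken as common, the noncentrality is n × 244.30/16.47².
- At n = 16 this is 14.41 and power is 88.4%. At n = 17 it is 15.31 and power is 90.5%.

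So 17 is the smallest n per group that gives this F test 90% power. With the pooled SD of 10.43, 8 per group would be enough. The article states no formula, so this origin is an inference.

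**The case against.** The strongest defence is that the phrase means at least one difference somewhere among the four groups. The planned analysis of continuous data is ANOVA, and 17 per group does give its omnibus test about 90% power with SD 16.47. On that reading the number is sound, even conservative, and only its description is loose. The possible origin stands, and it rules out saying that 17 follows from no sensible calculation. It does not rescue the sentence, which speaks of a difference between two groups and mentions no F test. On these figures the control group supplies 11.99² = 143.76 of the 244.30, or 59%, of the between-group sum of squares. A significant F test would therefore not show that frequencies differ from one another.

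Three stronger conclusions are tempting, and the documents do not support them.

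- **That the comparison of the highest with the lowest frequency is shown to be underpowered.** The arms are 1, 2 and 3 Hz. The 58% is for 2.5 vs 1 Hz, and no mean or SD is given for 3 Hz, so power for 3 vs 1 Hz cannot be computed.
- **That the high-versus-low hypothesis lacks power throughout.** On the same inputs, 2 vs 1 Hz has 97%.
- **That the trial is underpowered for its primary outcome.** These figures concern the NDI, listed as secondary. The primary outcome is a response rate, for which the section gives no planning values.

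It is also fair to say that the correction is one of wording and reporting.

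**Conclusion.** The power statement is wrong as written. On the plan's own inputs, three of the six pairs fall short of 90% by 27 to 47 percentage points, and complete data on all 22 per group would not close the gap. Of the three contrasts between frequencies, only 2 vs 1 Hz reaches the claimed power. If the true difference were that planned for 2.5 vs 1 Hz, the test would miss it about 42% of the time.

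The exact percentages assume a two-sided, unadjusted 0.05 and a Welch t test on each pair's own SDs. Which pairs fail does not depend on those choices. The conclusion applies to the NDI and to the planning frequencies. It is not an estimate of power for the 3 Hz arm or for the primary outcome.

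**What to change.** Keep the enrolment at 88 and rewrite the power statement:

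- Delete the claim of 90% power between any two groups.
- Say that the calculation is for the NDI, a secondary outcome, and that the 2.5 Hz planning data stand in for the 3 Hz arm, for which no mean or SD is available.
- State that 17 per group, at unadjusted two-sided 0.05, gives 95% for 2.5 Hz vs control, 97% for 2 vs 1 Hz and 99.6% for 2 Hz vs control, but 43% for 2.5 vs 2 Hz, 58% for 2.5 vs 1 Hz and 63% for 1 Hz vs control.
- If it was the actual basis, add that 17 per group gives about 90% power for the four-group F test with a common SD of 16.47.
- Commit to reporting the three low-power contrasts as estimates with 95% confidence intervals, and not to reading a non-significant result there as no difference.

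The cost is a less favourable stated power; no patients are added. Powering every pair instead would take about 54 completers per group, 216 in all before dropout, against 88 enrolled. Recruitment is already under way, so correcting the statement is the proportionate step.

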### Recruitment, randomization, allocation concealment, and blinding

The participants will be recruited through advertisements in hospital websites and bulletin boards. The participants who meet the inclusion criteria and have signed written informed consents will be randomly assigned to one of three MA manipulation groups (groups A–C) or the control group in a 1:1:1:1 ratio by central randomization performed by an independent statistician from the Tigermed Pharmaceutical Science and Technology Co., Ltd. Random numbers will be generated using the PROC PLAN of SAS 9.2 (SAS Institute Inc., Cary, NC, USA). Opaque sealed envelopes will be used to conceal the group to which participants have been allocated. Investigators who have contact with the participants should be unaware of the random allocation. To preserve masking, only the acupuncturists will have access to the treatment allocation. The participants, recruiters, and outcome assessors (the evaluator and the statistician) will be unaware of the group assignments.

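### The total of 88 adds 30% to the required number instead of dividing by 0.70, so at 30% dropout about 15 completers per group remain, not 17

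*Protocol article*

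**What the plan says.** The Sample size section of the protocol article lists a mean and standard deviation of the NDI score for four groups (2.5 Hz, 2 Hz, 1 Hz and control). It sets 90% power and a 5% type I error, and reports that "the calculated number of patients is 17". It then states: "Considering a 30% dropout rate, the total sample size required is 88 patients". It does not say whether 17 is per group or in total, and it does not print the formula used for dropout.

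The section on recruitment, randomization, allocation concealment and blinding assigns patients to one of three manipulation groups "or the control group in a 1:1:1:1 ratio". A total of 88 is therefore 22 per group.

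The Statistical analysis section plans an intention-to-treat (ITT) analysis with missing values filled by last observation carried forward (LOCF). The section on quality control and dropout criteria removes from the study patients who stop, miss treatment beyond a set limit, or breach the protocol.

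**The concern.** A dropout allowance is meant to leave the calculated number of patients after the expected losses. If a fraction d is lost, N randomised patients leave N × (1 − d), so the required N is n/(1 − d). Multiplying n by (1 + d) gives a smaller number that does not survive the loss it was meant to absorb. At d = 0.30 the two factors are 1.30 and 1/0.70 = 1.43, a visible gap.

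The printed total looks like the product of the first factor. If so, the article's own three figures (17, 30% and 88) cannot all hold, and a reader who relies on 88 to give 17 completers per group at 30% dropout is misinformed.

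**Working it through.** **Inputs.** All are in the Sample size section except the allocation ratio.
- Calculated number: 17. Dropout rate: 30%. Total: 88.
- Four arms at 1:1:1:1 (recruitment and randomization section), so 88/4 = 22 per group.
- NDI mean (SD): 2.5 Hz 82.28 (6.97); 2 Hz 86.73 (7.10); 1 Hz 76.50 (8.06); control 65.85 (16.47).
- Power 90%, type I error 5%. Sidedness is not stated.

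**Step 1: is 17 a per-group number?** A one-way ANOVA was tried with the four stated means and the largest stated SD, 16.47, as common SD.
- The grand mean is 77.84 and the deviations are 4.44, 8.89, −1.34 and −11.99. The sum of squares is 244.30, which divided by 4 gives 61.08.
- f² = 61.08/16.47² = 0.2252.
- With 17 per group, noncentrality = 4 × 17 × 0.2252 = 15.31 on 3 and 64 degrees of freedom. Power is 90.5%, and 17 is the smallest group size that reaches 90%.

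So 17 per group can be reproduced. The choice of 16.47 is an inference; the article does not state the method.

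**Step 2: reproduce 88.**
- Multiplying: 17 × 4 = 68, and 68 × 1.30 = 88.4. Per group, 17 × 1.30 = 22.1, taken as 22, and 22 × 4 = 88. This matches.
- Dividing: 68/0.70 = 97.1, so 98 before equalising the groups. Per group, 17/0.70 = 24.3, so 25, and 25 × 4 = 100. This does not match 88.

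A total of 17 over all groups leads to 88 by neither route.

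**Step 3: what 88 delivers.**
- At 30% dropout: 88 × 0.70 = 61.6 completers, or 15.4 per group. The shortfall is 17 − 15.4 = 1.6 per group, or 68 − 61.6 = 6.4 in total.
- Dropout that 88 can absorb: 1 − 17/22 = 22.7%.
- Gap in randomised patients: 100 − 88 = 12 (10 against 98).

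**Step 4: power on the set-up of Step 1.**

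| Completers per group | ANOVA power, common SD 16.47 |
|---|---|
| 17 | 90.5% |
| 15.4 | 87.0% |
| 15 | 85.9% |

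**Step 5: pairwise power** (Welch test, two-sided 5%, each pair's own SDs).

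| Contrast | 17 per group | 15 per group | 25 per group |
|---|---|---|---|
| 2 Hz vs control | 99.6% | 99.0% | above 99% |
| 2 Hz vs 1 Hz | 96.7% | 94.5% | above 99% |
| 2.5 Hz vs control | 95.1% | 92.1% | above 99% |
| 1 Hz vs control | 63% | 57% | 81% |
| 2.5 Hz vs 1 Hz | 58% | 53% | 76% |
| 2.5 Hz vs 2 Hz | 43% | 39% | 59% |

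No contrast crosses the 90% line between 17 and 15.

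**The case against.** **The analysis set.** Under ITT with LOCF, dropouts are imputed and analysed, so up to 22 per group enter the analysis. With 22 per group the ANOVA of Step 1 has about 97% power. This stands as a qualification: the figure of 15 counts completers, and a reader should not infer that only 15 per group will be analysed. It does not repair the sum. The article chose to inflate for dropout, which makes sense only if dropouts are treated as lost information, and carried-forward values can dilute an effect. The dropout section also speaks of removing such patients, so how they enter the analysis is not fully clear.

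**The readings are inferred.** Neither per group nor the inflation formula is printed. That is true, but nothing else among the stated figures leads to 88. One could read 30% as a margin simply added on top, which would make 88 consistent; the article calls it a dropout rate, so that reading is the weaker one.

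**The power loss depends on the set-up.** It does. If the common SD is the root mean square of the four SDs (10.43), ANOVA power at 15 per group is 99.9%; but that set-up needs only 8 per group for 90% and so does not give 17.

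**A stronger reading.** A reader might infer that the error costs the stated power even for contrasts that 17 per group would serve, or that it explains the low power of the weak contrasts. The article's own figures support neither. The three contrasts above 90% at 17 stay above it at 15. The other three are far below 90% at 17 and remain so with 25 completers per group, so their deficit is a separate problem.

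**Conclusion.** The discrepancy holds. The stated total does not deliver the stated number of completers at the stated dropout rate: 15.4 per group instead of 17, with 17 kept only up to about 22% dropout. The total consistent with 17 and 30% is 100.

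The effect is modest. Power falls to about 86% (87% at 15.4 per group) against the stated 90%, and this can be shown only for the overall four-group ANOVA with common SD 16.47. The conclusion rests on reading 17 as per group and on counting completers; the power figure also rests on the reconstructed ANOVA. It is a correction to a figure that readers rely on, not evidence that the design fails. Nor would the correction by itself establish power for the primary outcome: the calculation uses the NDI, listed under secondary outcomes, whereas the primary outcome is a response rate.

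**What to change.** Recruitment is under way, so the simplest course is to keep 88 and correct the sentence in the Sample size section. Suggested content: 17 is the number per group; 22 randomised per group preserve 17 completers per group for dropout up to 22%; at 30% dropout about 15 completers per group remain, with power of about 86% on the ANOVA calculation, if the sponsor confirms that this was the calculation used. Add that the ITT analysis with LOCF still includes dropouts through imputed values, so 15 refers to completers.

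If the sponsor prefers to keep both 17 completers and 30% dropout, the consistent total is 100 (25 per group), which means 12 more patients.

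The first option costs one corrected sentence and a slightly less favourable stated power. It changes neither enrolment nor analysis.
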